## SUMMARY

**Rationale:** Patients with obstetric complications like pre-eclampsia (PE), fetal growth restriction (FGR) or preterm pre-labor rupture of membranes (PPROM) often need hospitalization for fetal and maternal monitoring. Remote home monitoring has the potential to decrease the psychological and family burden of a hospital admission and to increase patient satisfaction while reducing health care costs due to a reduction in antenatal admissions. Previous research shows no indications that fetal home monitoring of selected complicated pregnancies imposes additional risks compared to in-hospital monitoring (1). Due to the limitations of conventional remote CTG monitoring like signal loss, electrophysiological cardiotocography (eCTG) has been developed and it is certified from 21 weeks of pregnancy onward. Since signal quality of eCTG in the preterm period – due to signal loss – is still unclear (2), the feasibility needs to be assessed first. The HASTA study will evaluate the feasibility of remote eCTG monitoring using non-invasive fetal electrocardiography (NI-fECG), Nemo Remote® Monitoring (NRM) in a hospital setting, as if the patient is at home (i.e., Home@Hospital setting). Automated interpretation of remote eCTG will be evaluated aiming to improve fetal monitoring and perinatal outcomes in the future. Additionally, this study will evaluate the feasibility of synchronized multimodal acquisitions of maternal and fetal measurements in a small population, aiming to understand the (patho)physiological mechanisms underlying cardiovascular function in pregnancy in the future.

**Objective:** To evaluate the feasibility of remote eCTG monitoring in complicated pregnancies between 32-37 weeks in a Home@Hospital setting. Secondary objectives are to evaluate automated interpretation of remote eCTG monitoring and to evaluate perinatal and maternal outcomes, patients and healthcare professionals satisfaction, and costs. Additional objective is to evaluate the feasibility of synchronized multimodal acquisitions of maternal and fetal measurements.

**Study design:** A single center interventional prospective cohort study.

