#### **4.4 Sample size calculation**

In a previous cohort study for conventional remote CTG monitoring, 4% of all tracings needed repetition (562 out of 12,649) and 0.9% (N=111) of the CTGs had to be repeated in the hospital. The success rate at first trace was 95.5% and after repetition 99% (28) .

A success rate of 90% is considered clinically sufficient based on previous studies (28-30) and HCPs' opinion. Only the first day of remote eCTG measurements will be used for determination of the feasibility by assessing the signal quality and success. If the remote eCTG measurement is technically insufficient but reassuring – according to current clinical policy – it can be repeated once at the same day and still be considered successful. Calculated on 90% chance of success according Wilson standard error of proportions (CI95% > lower limit of 82.5%), 60 subjects are needed for inclusion in this cohort study.

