## 9. STATISTICAL ANALYSIS

### 9.1 Primary study parameter(s)

Primary data statistical analyses will be performed using SPSS version 29 (IBM Corp., Armonk, NY, USA) and SAS software version 9.4 (SAS Institute Inc., Cary, NC, USA). Signal quality will be defined as the percentage of time (minutes) in which the remote eCTG device delivers an FHR value. Signal quality will be determined for each patient. Mean, SD, and 95% confidence interval (CI) of the mean success rate will be calculated using a one-sample t-test. The one-way ANOVA analog, Kruskal-Wallis test will be used in when no normal division of outcomes is found. Success rate will be defined as the number and percentage (N/%) of remote eCTG registration the first day of inclusion with at least 30 minutes interpretable signal quality and/or less than 20% signal loss during 30 to 90 minutes measurement (see section 7.1.1).

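### Section 9.1 analyses a yes/no success rate in one cohort with a one-sample t-test and a Kruskal-Wallis fallback; neither gives a sound interval for it

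*Protocol*

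**What the plan says.** Section 9.1 begins with a continuous measure: "Signal quality will be defined as the percentage of time (minutes) in which the remote eCTG device delivers an FHR value", determined for each patient. It then turns to the primary outcome: "Mean, SD, and 95% confidence interval (CI) of the mean success rate will be calculated using a one-sample t-test". The fallback follows: "The one-way ANOVA analog, Kruskal-Wallis test will be used in when no normal division of outcomes is found". The section closes by defining the outcome: "Success rate will be defined as the number and percentage (N/%) of remote eCTG registration the first day of inclusion" that meets the signal criteria.

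The design is described in the Summary as "A single center interventional prospective cohort study". Section 7.2 gives randomisation and allocation as not applicable. Section 9.1 names no groups.

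The sample size in section 4.4 rests on a different method: "Calculated on 90% chance of success according Wilson standard error of proportions (CI95% > lower limit of 82.5%), 60 subjects are needed". On repeats, the same section says of a technically insufficient but reassuring recording that "it can be repeated once at the same day and still be considered successful".

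**The concern.** Each participant either succeeds or fails on the first inclusion day. A t-interval on such 0/1 data is symmetric around the observed proportion and takes its width from that proportion alone. It therefore ignores the 100% ceiling and shrinks to nothing as failures become rare. A feasibility study hopes to land in that region: section 4.4 cites 95.5% at first trace and 99% after repetition for conventional remote CTG.

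The fallback makes matters worse. Its trigger is non-normality, which 0/1 data always show, and the test it leads to compares groups that this study does not have.

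At stake is the uncertainty statement around the only primary result, and above all the lower limit, which is the quantity used to size the study. The t-interval errs there in the favourable direction.

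**Working it through.** **Inputs.** n = 60, planned rate 90% and lower limit 82.5% (section 4.4); one yes/no outcome per participant (sections 2.1, 4.4 and 9.1); one cohort (Summary).

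**The plan's own figure.** With the simple normal (Wald) formula, n = 1.96² × 0.9 × 0.1 / 0.075² = 61.5, so 62, close to the stated 60; the Wald lower limit at 54/60 is 82.4%. The two-sided 95% Wilson lower limit at 54/60 is 79.9%, and reaching 82.5% at an observed 90% would need n = 99. So 60 is roughly reproduced, but not by the method that section 4.4 names.

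**Formulas for x successes out of 60, p = x/60.**
- t-interval: p ± t(0.975; 59) × √(p(1−p)/59), with t = 2.001.
- Wilson: centre (p + z²/2n)/(1 + z²/n); half-width z√(p(1−p)/n + z²/4n²)/(1 + z²/n), with z² = 3.841.

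**Worked at 54/60.** t: √(0.09/59) = 0.0391; × 2.001 = 0.0782; interval 82.2% to 97.8%. Wilson: centre (0.9 + 0.0320)/1.0640 = 0.876; half-width 0.077; interval 79.9% to 95.3%.

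| Successes | t-interval | Wilson |
|---|---|---|
| 54/60 | 82.2% to 97.8% | 79.9% to 95.3% |
| 55/60 | 84.5% to 98.9% | 81.9% to 96.4% |
| 56/60 | 86.8% to 99.8% | 84.1% to 97.4% |
| 57/60 | 89.3% to 100.7% | 86.3% to 98.3% |
| 59/60 | 95.0% to 101.7% | 91.1% to 99.7% |
| 60/60 | 100% to 100% | 94.0% to 100% |

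From 54 to 57 successes the t lower limit is 2.3 to 3.0 points above Wilson's, and the gap widens beyond that. The t limit first clears 82.5% at 55/60, Wilson's at 56/60.

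**Exact coverage of the nominal 95% intervals** (binomial probabilities summed over the outcomes whose interval contains the true rate, n = 60):

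| True rate | t-interval | Wilson |
|---|---|---|
| 90% | 94.1% | 95.2% |
| 92% | 95.1% | 94.5% |
| 94% | 87.9% | 97.4% |
| 95% | 95.1% | 97.0% |
| 97% | 83.7% | 96.6% |
| 98% | 70.1% | 96.8% |

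**Direction of the misses at a true 90%.** The t lower limit exceeds 90% from 58/60 upward; P(X ≥ 58) = 5.3%, against a nominal 2.5%. Wilson's exceeds it only from 59/60; P(X ≥ 59) = 1.4%.

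**How often the t-interval passes 100% or has no width.** 14% of trials at a true 90%, 65% at 95%.

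**Fallback.** Kruskal-Wallis has (number of groups − 1) degrees of freedom. With one group that is 0, and the software call fails. With two or more groups it returns a between-group p-value, not a success rate or an interval.

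**The case against.** The best defence is that the t-test was meant for signal quality. The sentence defining that measure stands just before; it is a continuous percentage per patient, for which a mean, SD and one-sample t-interval are reasonable. Success is later given as a number and percentage, which needs no t-test. On this reading one phrase is misplaced, and the claim that the fallback always applies falls away. This is plausible and supports separating the two measures in the text. But the sentence says success rate, and Kruskal-Wallis on one group is no more usable for signal quality. It could be run across the diagnostic subgroups mentioned in section 9.2, but section 9.1 does not say so, and it would still not estimate the overall rate.

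Three further points stand and limit the concern. At the planned 90%, coverage is nearly right. The rates close to 100% in section 4.4 come from conventional CTG, while section 6.4.4 warns of more signal loss with this device from 27 to 36 weeks. And 60 follows from Wald arithmetic, to which the t-interval is close, so a Wilson analysis agrees with the named method in section 4.4 but not with the calculation behind the number.

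A reader might also infer from the word registration in section 9.1 that failed first recordings enter the denominator, which would pull the rate down. The documents do not support this. Section 2.1 assesses the first or, when indicated, the second recording; section 4.4 counts success after one repeat and sizes the study in subjects; section 7.3.2 declares failure only after repetition. The unit is the participant, and the noun is merely loose.

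**Conclusion.** As written, the method for the primary interval is wrong and the fallback is unusable. Because section 9.1 fixes the method, the fallback and its trigger, this is not a detail left for a statistical analysis plan: a plan that followed it would inherit the error, and one that departed from it would contradict the protocol.

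The size is moderate at the planned rate: a lower limit 2.3 points too favourable at 54/60, with 94.1% coverage. It becomes serious near 100%, with impossible or zero-width intervals and coverage of 70.1% at 98%. Coverage does not decline steadily, since it is 87.9% at 94% and 95.1% at 95%.

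Two stronger readings should be resisted. The primary result is not lost, because the number and percentage survive; only the interval is affected. Nor would a study decision be reversed: section 4.4 says "A success rate of 90% is considered clinically sufficient based on previous studies" and uses 82.5% as a precision target, but ties no go/no-go rule to the lower limit, and the two methods fall on opposite sides of 82.5% only at exactly 55/60.

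The figures assume 60 analysed participants with one independent outcome each.

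**What to change.** In section 9.1:
- Report the number and percentage of participants with success on the first inclusion day (first or, when indicated, repeated recording, as in sections 2.1 and 4.4), with a two-sided 95% Wilson interval.
- Delete the t-test and Kruskal-Wallis for success.
- If a mean, SD and t-interval are wanted, attach them explicitly to signal quality.
- Replace registration by participants in the definition of the success rate.

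In section 4.4, restate the lower limit: with 60 participants and 54 successes the Wilson interval is 79.9% to 95.3%, so 82.5% does not hold under the named method.

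The change costs a rewording and needs no new data or procedures. The price is a reported lower limit about 2 to 3 points lower for results from 54 to 57 out of 60, and an open statement that 60 participants give less precision than section 4.4 now says.

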**Study population:** Pregnant patients (N=60) >18 years old with a singleton, high-risk pregnancy from 32 until 37 weeks of gestational age. High-risk is defined as: diagnosed with PE, FGR, PPRM, or others with an indication for fetal monitoring at least twice a week, these patients are eligible for inclusion in this study. The main exclusion criteria are: suspected labor within 48 hours, severe pre-eclampsia, umbilical artery Doppler with absent- or reversed flow, external- or implanted electrical stimulator and language barrier.

**Intervention:** Remote eCTG monitoring (using Nemo Remote®), daily in a Home@Hospital setting for 30-90 minutes, or at least twice weekly at the outpatient clinic. Monitoring duration depends on signal quality and interpretability of the eCTG tracing, and lasts at least 30 minutes, and will be ceased after 90 minutes if the eCTG signal quality and/or interpretability is then still insufficient. In 24 patients ultrasound clips of 2 x 5 minutes of the uterine and umbilical artery Doppler will be collected simultaneously to the eCTG measurements.

**Main study parameters/endpoints:** Primary outcome: The percentage of successful eCTG measurements in a Home@Hospital setting. This will be defined as the necessity to switch to conventional CTG based on the amount of signal loss. Secondary outcomes: Automated interpretation of the eCTG, maternal and perinatal outcomes, patient and healthcare professional satisfaction and costs. Additional outcome: Feasibility of synchronized multimodal acquisitions of maternal and fetal measurements.

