### 3. STUDY DESIGN

The study will be conducted as a single center prospective cohort study between November 2024 and April 2026, aiming to include 60 eligible patients between 32 and 37 weeks of gestational age. The study is situated at the obstetric department of the Máxima Medical Center (MMC), a secondary and tertiary maternity care unit. However the aim of this study is to evaluate home monitoring in a hospital setting (Home@Hospital), only the use of remote eCTG through a NRM connection will differ from the standard care. A detailed description of the study population including sample size calculation, treatment of subjects, methods and statistical analysis, is provided in chapters 4,5,7 and 9. For study design and study procedures see Figure 2. The study will be registered on 'ToestingOnline' and 'www.clinicaltrials.gov'.

[figure not shown]

Figure 2. Flowchart of the HASTA prospective cohort design and study procedures.

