- Once the eCTG measurement is considered successful – or when the maximum of 90 minutes has exceeded – the HCP will send a message in the Luscii app® and will contact the participant by telephone a few minutes later, the time they have stopped the remote eCTG measurement. All findings will be discussed with the participant and completed in the patients' file in HiX. In addition, the HCP will visit the participant in the hospital room.
- When eCTG measurement is not successful but reassuring, the measurement will be repeated the same day on a moment agreed between participant and HCP (PA).
- When eCTG measurement is not interpretable after repetition on the first day of inclusion, eCTG will be defined not successful – primary outcome – and a switch to conventional CTG will take place. Equally to routine care, in- hospital care is needed and home- monitoring will not be possible.
- When after an additional clinical visit by the HCP (PA) “unscheduled consult” at participants room for other reasons than signal quality concerns (e.g. contractions, reduced fetal movements, patients concerns), without indication for hospitalization – eCTG adequate and reassuring – participants can continue “home monitoring” through eCTG like it will be once home monitoring is implemented in the future. No switch to conventional CTG will be needed. This additional visit will be recorded as part of the patient journey for later cost analysis purposes (*Figure 11, Table 2*).
- As long as remote eCTG measurements are successful, participants will continue the study interventions until discharge, delivery or when 37 weeks is reached. At any moment – when demanded by the participants or by the HCP – a switch to conventional CTG will be made.
- When reached a GA of 37 weeks, after delivery or at discharge, participants will be asked to fill in a second digital questionnaire (5.1, 7.3.3), and at 4 weeks after delivery a third questionnaire.

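### Section 9.1 gives the yes/no primary outcome of a single cohort a one-sample t-test with a Kruskal-Wallis fallback, so the success rate has no suitable interval method

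*Protocol*

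**What the plan says.** The Protocol describes one cohort without a comparator. Section 3 says "The study will be conducted as a single center prospective cohort study", and section 7.2 marks randomisation and allocation as not applicable. The Summary gives the primary outcome as "The percentage of successful eCTG measurements in a Home@Hospital setting". Each woman has one result, from the first day, with at most one repeat. For hospitalised participants section 7.3.2 says "When eCTG measurement is not interpretable after repetition on the first day of inclusion, eCTG will be defined not successful", and it has the same rule for outpatients.

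Section 9.1 first defines signal quality, a continuous percentage of time for each patient. It then says "Mean, SD, and 95% confidence interval (CI) of the mean success rate will be calculated using a one-sample t-test", followed by "The one-way ANOVA analog, Kruskal-Wallis test will be used in when no normal division of outcomes is found". It closes with "Success rate will be defined as the number and percentage (N/%) of remote eCTG registration the first day of inclusion".

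Section 4.4 takes 90% as the success rate and sizes the study "according Wilson standard error of proportions (CI95% > lower limit of 82.5%), 60 subjects are needed".

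**The concern.** The primary result is a single binomial proportion, and neither method named in section 9.1 is designed for one. The interval around the success rate is the main product of this feasibility study, and the lower limit matters most because section 4.4 sizes the study on it.

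If section 9.1 is followed to the letter, the normality condition fails for any yes/no outcome. The analyst is then sent to a test that cannot be run on one sample and yields a p-value, not an interval. If the condition is ignored and the t interval is used, the lower limit is optimistic and the upper limit can pass 100%. Either way the interval method would in practice be chosen after the count is known.

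**Working it through.** **Inputs.** n = 60, planned success rate 90%, two-sided 95% interval, lower-limit target 82.5% (section 4.4). One success or failure per woman in one group (Summary, sections 3, 7.2, 7.3.2). Quantiles: z = 1.960; t with 59 df = 2.001.

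**The plan's own figure first.**
- Wald: n = 0.9 × 0.1 × (1.96/0.075)² = 61.5, so 62, close to the stated 60. At n = 60 the Wald lower limit is 0.9 − 1.96 × √(0.09/60) = 82.4%.
- Two-sided Wilson at 54/60: z²/n = 0.0640. Centre = (0.9 + 0.0320)/1.0640 = 0.8759. Half-width = 1.96 × √(0.0015 + 0.000267)/1.0640 = 0.0774. Interval 79.9% to 95.3%. A Wilson lower limit of 82.5% at an observed 90% needs about 99 women.

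So 60 women and 82.5% fit a Wald calculation, not the Wilson interval that section 4.4 names. The Protocol does not show its calculation, so Wald is an inference from the numbers.

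**The t interval on 0/1 data.** SD = √(n·p(1−p)/(n−1)); limits = p ± 2.001 × SD/√n. At 54/60: SD = √(60 × 0.09/59) = 0.3025; half-width = 2.001 × 0.3025/7.746 = 0.0782; interval 82.2% to 97.8%.

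| Successes of 60 | t interval | Wilson interval | Difference in lower limit |
|---|---|---|---|
| 54 | 82.2 to 97.8% | 79.9 to 95.3% | 2.3 points |
| 55 | 84.5 to 98.9% | 81.9 to 96.4% | 2.5 points |
| 57 | 89.3 to 100.7% | 86.3 to 98.3% | 3.0 points |
| 60 | 100 to 100% | 94.0 to 100% | 6.0 points |

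The t upper limit exceeds 100% at 57, 58 and 59 successes only; at 60 it equals 100% with zero width. If the true rate is 90%, 57 to 59 successes have probability 14%; at 95%, 60%.

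**Exact behaviour.** For each true rate p, the Binomial(60, p) probabilities were summed over the counts whose interval contains p (coverage), and over the counts whose lower limit lies above p (lower-tail error, nominal 2.5%).

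| True rate | t coverage | Wilson coverage | t lower-tail error | Wilson lower-tail error |
|---|---|---|---|---|
| 90% | 94.1% | 95.2% | 5.3% | 1.4% |
| 94% | 87.9% | 97.4% | 11.8% | 0% |
| 95% | 95.1% | 97.0% | 4.6% | 0% |
| 97% | 83.7% | 96.6% | 16.1% | 0% |

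The rates above 90% are relevant because section 4.4 cites 95.5% at first trace and 99% after repetition for conventional remote CTG.

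**The fallback.** Kruskal-Wallis compares distributions between independent groups. With the 60 outcomes entered as one group, the software routine stopped with an error. Diagnosis subgroups appear only in section 9.2, under the secondary parameters.

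**The case against.** The strongest defence is that the t-test sentence belongs to signal quality. The two sentences before it define that continuous variable, and a mean, an SD and a normality check all suit it. The success rate is defined afterwards as a count and percentage. This reading is plausible, and under it the t-interval figures above would not apply to the primary outcome. But the sentence names the success rate, so the reading is not secure. It also does not rescue the section: Kruskal-Wallis is not a one-sample substitute for a t-test, and the primary proportion would then have no stated interval method.

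A second defence is that the t interval does little harm at the planned rate. That stands for two-sided coverage, which is 94.1% at 90% and 95.1% at 95%. A reader might infer from the faults above that the t interval is invalid throughout; those figures do not support that. The faults are the uneven tails, the impossible limits and the erratic coverage at higher rates.

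A reader might also infer that the choice of method decides whether the study succeeds, because at 55/60 the t lower limit (84.5%) is above 82.5% and the Wilson limit (81.9%) is below it. The Protocol does not support this. Section 4.4 uses 82.5% as a sizing target, neither 4.4 nor 9.1 makes it a pass/fail rule, and the rate called clinically sufficient is 90%.

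Leaving the matter to a statistical analysis plan is no answer, because the Protocol names specific methods and they do not fit.

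**Conclusion.** The point holds on either reading of section 9.1. Read literally, the primary proportion is sent to a test that cannot give its interval. Read charitably, it has no interval method and signal quality has an unusable fallback. The count and percentage themselves are unaffected.

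If the t interval is used at n = 60, its lower limit is 2.3 to 3.0 points more favourable than Wilson at 54 to 57 successes, and its lower-tail error at a true 90% is about double nominal. These figures assume one independent result per woman and 60 women analysed.

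It would be wrong to conclude that section 9.1 merely departs from a Wilson calculation that produced N = 60. Wilson is the name used in section 4.4, but the numbers there agree with Wald, whose lower limit at 54/60 (82.4%) is almost the t limit (82.2%). Changing section 9.1 alone would therefore leave the planned 90% short of the limit stated in section 4.4.

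**What to change.** In section 9.1:
- Report the primary outcome as women with success over women included, with a two-sided 95% Wilson (or exact) interval.
- Delete the t-test and Kruskal-Wallis for this outcome.
- Describe signal quality in its own sentence, by mean and SD or median and IQR, with a suitable one-sample interval.
- Keep Kruskal-Wallis only where named independent subgroups are compared.

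In section 4.4, at the same time: keep N = 60 and state that an observed 54/60 gives a two-sided 95% Wilson interval of 79.9% to 95.3%, so that the lower limit reads about 79.9% instead of 82.5%. Keeping 82.5% under Wilson would need about 99 women.

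Cost: a few sentences, with no extra data or patients if N = 60 is kept. The reported lower limit becomes about 2 to 3 points less favourable at 54 to 57 of 60. The change should be made before the first-day results are analysed.

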### Remote electrophysiological cardiotocography monitoring (eCTG) – Nemo Remote® (NRM)

Due to the limitations of conventional CTG monitoring, extensive research has been carried out to develop new, non-invasive, monitoring methods. Remote eCTG – including NI-fECG – monitoring has shown to be a very promising technique (17-20). This technique uses a wireless and beltless electrode patch that is placed on the maternal abdomen (Figure 1). It monitors fetal heart rate (FHR) by fetal electrocardiography (fECG), maternal heart rate by maternal electrocardiography, and the electrical activity of the uterine muscle by electrohysterography (EHG) (21-24). The electrophysiological recordings are hardly affected by maternal or fetal movement or abdominal wall thickness, as they are transferred through conduction of electrical signals across the underlying tissues (13, 25). Furthermore, the wireless electrode patch on the maternal abdomen gives patients the ability to move (16). The HASTA study will evaluate the feasibility of self-administered home monitoring in a Home@Hospital setting for a selected groups of complicated pregnancies. Feasibility will be evaluated by assessing the success rate (percentage of successful measurements) of remote eCTG, and whether no switch to conventional CTG due to interpretability is needed. Success rate is defined as maximum of 20% signal loss of total recorded time or at least 30 minutes of sufficient CTG interpretability. For further description see sections 2.1 and 7.1.1.

[figure not shown][figure not shown]

*Figure 1. eCTG including NI-fECG – Nemo Remote® (NRM)*

Furthermore, the FHR obtained from the fetal ECG measurements collected through NRM in this study will be used to check if the algorithm of the FHR – developed during labor – can also benefit for premature fetus. Automated interpretation of fetal monitoring could lead to improved prevention in the future. In addition, the effects of self-administered remote eCTG monitoring in a Home@Hospital setting on maternal and perinatal outcomes, patient and HCP satisfaction, and costs will be evaluated.

Besides feasibility of eCTG, this study will additionally evaluate the feasibility of synchronized multimodal acquisitions of maternal and fetal measurements as a first step towards the development of a prediction model.

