## **2. OBJECTIVES**

### **2.1 Primary objective**

The primary objective of this study is to assess the percentage of successful self-administered remote eCTG (including NI-fECG ) measurements in a Home@Hospital setting. This will be defined based on the percentage of signal loss and total duration of adequate registration and will be assessed on the first or – when indicated – the second eCTG measurement on the first day of inclusion. When the first remote eCTG measurement is reassuring but insufficient, the measurement will be repeated the same day.

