## 7. METHODS

### 7.1 Study parameters/endpoints

#### 7.1.1 Main study parameter

To assess the primary objective of successful remote eCTG monitoring, definitions of successful measurement are as follows:

- Minimum of 30 minutes eCTG registration (32);
- Including overall a maximum of 20% signal loss (32);
- Sufficient interpretability according to HCPs clinical interpretation, if not maximum extended until 90 minutes when reassuring but insufficient.

Criteria defining a successful measurement is described in a standard operating procedure (SOP) and will be available for (trained) HCPs at the hospital to avoid prematurely closing of the eCTG registration. The precise duration of monitoring in minutes, the amount of signal loss in percentage and the duration of signal loss in minutes will be derived from the recordings during the analysis phase of the project, i.e. not during the measurements.

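### The primary endpoint is defined inconsistently: Section 7.1.1 reads as cumulative, the introduction says *or* and Section 9.1 says *and/or*, so the same recordings can give different success rates

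*Protocol*

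**What the plan says.** Three places in the protocol state what counts as a successful measurement.

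- **Section 7.1.1 (main study parameter)** lists three criteria: "Minimum of 30 minutes eCTG registration (32"; "Including overall a maximum of 20% signal loss (32"; and "Sufficient interpretability according to HCPs clinical interpretation, if not maximum extended until 90 minutes when reassuring but insufficient". (The number 32 is a literature reference.) No *and* is written. The list form, and the word that ties the loss limit to the registration, make it cumulative.
- **Section 1 (introduction, part on Nemo Remote)**: "Success rate is defined as maximum of 20% signal loss of total recorded time or at least 30 minutes of sufficient CTG interpretability".
- **Section 9.1 (primary analysis)**: "with at least 30 minutes interpretable signal quality and/or less than 20% signal loss during 30 to 90 minutes measurement".

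The introduction and 9.1 both refer to 7.1.1, but neither matches it.

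Three other places add to this. Section 2.1 gives no thresholds: "This will be defined based on the percentage of signal loss and total duration of adequate registration". The summary says of the primary outcome: "This will be defined as the necessity to switch to conventional CTG based on the amount of signal loss". Section 7.3.2, for hospitalised participants and in near-identical words for outpatients, attaches the primary-outcome label to a bedside finding: "When eCTG measurement is not interpretable after repetition on the first day of inclusion, eCTG will be defined not successful".

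The rule that a reassuring but insufficient first recording may be repeated once on the same day is consistent between Sections 2.1 and 4.4 and is not part of the problem.

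**The concern.** The study has one arm, and its main result is one proportion set against 90%. No comparator absorbs an ambiguity in the numerator.

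Section 9.1 departs from 7.1.1 in three ways. *And/or* is not a rule that can be programmed. The loss limit changes from at most 20% to less than 20%. The 30 minutes change from registered to interpretable minutes. The introduction goes further and makes meeting either limb enough.

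Recordings on which the rules disagree are plausible here. Poor traces may be extended to 90 minutes. Section 6.4.4 warns of more fetal heart rate (FHR) signal loss from 27 to 36 weeks, and the study enrols from 32+0 to 36+6 weeks. Duration and signal loss are derived only in the analysis phase (7.1.1), so as the protocol stands the rule could be settled once recordings are in hand.

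Section 7.1.2 also uses 7.1.1 for success after a switch to conventional CTG and for prematurely closed recordings. Primary and secondary results could therefore rest on different definitions.

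**Working it through.** **Figures in the plan.** Section 4.4 gives 60 participants and a clinically sufficient success rate of 90%; 0.90 × 60 = 54 successes. The protocol gives no estimate of how many recordings would be classified differently.

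**1. The same recordings under each rule.** Section 9.1 defines signal quality as the share of time with an FHR value. Let T be the recording length in minutes and L the share of time lost; minutes with an FHR value = T × (1 − L). The HCP's judgement is an assumed input. For the 30-minute limb of the introduction and 9.1, minutes with an FHR value stand in for interpretable minutes, which is also an assumption.

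| Recording | Minutes with FHR value | 7.1.1 | Introduction (*or*) | 9.1 as *and* | 9.1 as *or* |
|---|---|---|---|---|---|
| A: 60 min, 40% loss, HCP satisfied | 60 × 0.60 = 36 | fail | success | fail | success |
| B: 90 min, 66% loss, HCP satisfied | 90 × 0.34 = 30.6 | fail | success | fail | success |
| C: 30 min, 10% loss, HCP satisfied | 30 × 0.90 = 27 | success | success | fail | success |
| D: 30 min, exactly 20% loss, HCP satisfied | 30 × 0.80 = 24 | success | success | fail | fail |
| E: 40 min, 15% loss, HCP not satisfied, switched | 40 × 0.85 = 34 | fail | success | depends on who judges interpretability | success |

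A and B show the *or* reading as the more lenient. C shows that even the *and* reading of 9.1 is not 7.1.1, because the two count different minutes: at 20% loss a recording must last 30 / 0.80 = 37.5 minutes to hold 30 minutes of signal. D is the boundary case. E passes the introduction on the loss limb alone, yet fails 7.1.1 on HCP judgement and counts as a failure under the summary and, if not interpretable after repetition, under 7.3.2.

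**2. Loss tolerated at a given length**, under the same assumption. Section 7.1.1: 0.20 × T. *Or* reading: the larger of 0.20 × T and T − 30.

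- T = 45: 9 v 15 minutes (20% v 33.3%)
- T = 60: 12 v 30 minutes (20% v 50%)
- T = 90: 18 v 60 minutes (20% v 66.7%)

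**3. Effect on the headline rate.** Suppose 54/60 succeed under *or*, and some participants pass *or* but fail 7.1.1. The number is not in the documents, so a range is shown (Wilson 95% CI):

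| Discordant participants | 7.1.1 result | 95% CI |
|---|---|---|
| 0 | 54/60 = 90% | 79.9 to 95.3 |
| 3 (5%) | 51/60 = 85% | 73.9 to 91.9 |
| 6 (10%) | 48/60 = 80% | 68.2 to 88.2 |
| 9 (15%) | 45/60 = 75% | 62.8 to 84.2 |
| 12 (20%) | 42/60 = 70% | 57.5 to 80.1 |

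Three participants are enough to move the point estimate from the benchmark to 5 points below it.

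**The case against.** **Section 7.1.1 is the designated definition, and the other sections point to it.** This narrows the point. The summary is a short restatement, and 7.3.2 is mainly bedside workflow, so a reader who counts five rival definitions overstates the case. The core conflict is between 7.1.1, the introduction and 9.1. The cross-references do not cure it: 9.1 is the analysis rule, it restates the criterion differently, and nothing says which version governs.

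**Interpretable minutes are not the same as minutes with an FHR value.** This stands. In 7.1.1 interpretability is the HCP's judgement, and nothing suggests an HCP would accept a 90-minute trace with two thirds lost. A reader might infer that the *or* reading makes the 20% limit almost inactive; that holds only under the stated assumption. Recording A does not depend on an extreme trace, and E passes on the loss limb whatever is counted as interpretable.

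**The size is unknown.** This also stands. A reader might infer that the cumulative rule falls below 90% and the *or* rule above it. For a first recording with loss assumed Beta-distributed (concentration 4), mean loss of 10% gives 82.7% under the cumulative rule and above 99% under *or*. Mean loss of 5% gives 92.4% even under the cumulative rule. That illustration also leaves out the same-day repeat and the HCP's judgement. The documents give no loss distribution for this device at these weeks, so neither direction relative to 90% is established.

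**The SOP, or a separate analysis plan, may settle the rule.** Neither is at hand. A choice made after seeing data is therefore a possibility left open by the protocol text, not something it shows to be intended. The protocol would still contradict itself.

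**Conclusion.** The inconsistency is real and must be fixed: on the current text the primary endpoint is not determined. That conclusion rests on the wording alone, with one inference, that the list in 7.1.1 is cumulative. Recordings can be classified in opposite ways, in both directions.

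The 50% and 66.7% tolerances at 60 and 90 minutes need the further assumption that every minute with an FHR value is interpretable. The effect on the result cannot be derived from the documents; the documented sample size shows only that three discordant participants suffice to move 90% to 85%. The difference between less than 20% and at most 20% matters only at exactly 20%. The summary and 7.3.2 are secondary, though the summary's wording, read literally, describes failure and not success.

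**What to change.** Use the 7.1.1 criteria as the single analysis definition in Section 9.1, the introduction and the summary. A participant is a success if the first recording on the first inclusion day or, where done, the same-day repeat meets all of:

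1. at least 30 minutes registered;
2. at most 20% of recorded time without an FHR value;
3. judged interpretable by the HCP.

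Write the *and* into 7.1.1, and delete *or* and *and/or* elsewhere. Report the rate with 30 interpretable minutes regardless of loss as a named sensitivity result, stating how interpretable minutes are measured. Switches to conventional CTG and prematurely closed recordings are already secondary parameters in 7.1.2 and need no new outcome.

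For 7.3.2, ask only that its primary-outcome label be reconciled with 7.1.1, noting that signal loss is derived in the analysis phase and is not measured at the bedside. The rule for repeating or switching is clinical management, and no change to it is proposed here.

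The cost is rewording in these places and one extra tabulation; the sample size is unchanged. There are two downsides. The headline rate may be lower than under the *or* reading, and a trace accepted at the bedside may later fail on signal loss without having been repeated. The report should count such cases.
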